### Analysis

The main analyses will be by intention to treat. We will compare the incidence of ArCD in:

- 1,000 persons treated with MET with the 1,000 treated with placebo
- 1,000 persons randomized in the lifestyle intervention group with the 1,000 in the control group
- 500 persons treated with both MET and lifestyle intervention with the remaining 1,500
- 1,500 persons treated with MET or lifestyle intervention with the 500 without any treatment
- 500 persons treated with both MET and lifestyle intervention with the 500 without any treatment.

In ancillary companion studies we will analyse the epigenetic pattern at baseline, and its change over one year of treatments, in participants who developed, or did not develop, ArCD, as well as in participants who succeeded, or did not succeed, to make MetS regress (with or without MET or lifestyle changes).

**Power computations** have been based

- a) on expected mortality and ArCD incidence in the study area in men and women aged 55 or more (assuming the same age distribution as the general population),
- b) on the assumption that MetS is associated with 1,5 higher incidence of ArCD (3 times more for diabetes);
- c) on the hypothesis that the planned interventions may reduce ArCD incidence by 25 or 33%; d) on a 3.5-year average follow-up (within the 5-year study period); and,
- e) alpha error = 0.05.

Hypothesising to recruit 1000 persons with MS per year in the first two years, excluding the person-years accumulated in the recruitment year, plus 200 persons to compensate the power loss due to expected attrition (for mortality and decisions to stop participation), we would expect about 174 deaths, 175 cancers, and 119 major cardiovascular events (myocardial infarction and stroke), and 219 cases of diabetes, summing up to over 500 incident cases of major ArCD.

We will have, for 33% (and, respectively, 25%) reduction in the cumulative incidence of major ArCD (cardiovascular + diabetes + cancer):

- 99% (92%) power to compare 1,000 persons treated with metformin with 1,000 receiving placebo (or 1,000 persons with or without active lifestyle intervention)
- 97% (84%) power to compare 500 persons treated with both metformin and lifestyle intervention with respect to the other 1,500.
- 89% (65%) power to compare 500 persons with both interventions with 500 with none

Comparing 1,000 treated and 1,000 non-treated persons, we will have 69% power to detect a significant 33% difference in total mortality, or in the cumulative incidence of cancer, and 98% power to detect a 33% difference in the cumulative incidence of diabetes (85% for 25% reduction).

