**Inclusion criteria:**

Age 55-74, waist circumference equal or greater than 85 cm for women and 100 cm for men, plus at least two other factors among those defining the MetS

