**Exclusion criteria:**

- Diagnosed diabetes (or baseline fasting glycemia above 7mmol/L at baseline examination)
- Cancer (except skin carcinoma) diagnosed in the last 5 years, or under treatment
- Excessive frailty: in absence of agreed-upon measurements parameters and cutoff points, we will exclude subjects under the lower 5th percentile of the muscular mass distribution estimated by impedance in previous studies
- Conditions that contraindicate the use of MET because might favour lactic acidosis
  - Renal, cardiac, hepatic, or respiratory insufficiency
  - Serum creatinine <124µmol/L, or proteinuria at baseline examination
  - Current treatment with K-sparing diuretics, or with proton pump inhibitors
  - Excessive alcohol consumption
- Distressing side effects of MET treatment. Nausea and diarrhoea typically occur in about one third of patients receiving MET for the first time at full dose. To avoid dropouts for gastrointestinal discomfort we will treat all volunteers with half the planned dose for one month in order to exclude intolerant subjects before randomization. Participants randomized in the intervention group will continue to take half a dose for one month and then shift to the full dose.

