#### Inclusion criteria:

1. waist circumference > 85 cm for women and >100 cm for men
2. age between 55 and 74
3. no diagnosis of cancer in the last 5 years (except skin carcinomas)
4. no diabetes (IDDM and NIDDM),
5. no kidney insufficiency
6. no acute or chronic hepatitis
7. no diagnosis of coronary heart disease, myocardial infarction, stroke, hearth failure
8. no neurodegenerative disease
9. not under treatment with the following drugs:
  - Cimetidine, Ranitidine
  - Sulfamethoxazole + Trimetoprim (Bactrim, Chemitrim, Eusaprim)
  - Nifedipine (Adalat, Nifedidor, Nifasal, Nipin, Fenidina, Euxat, Coral, Citilat)
  - Furosemide (Lasix)
  - Diuretics with K retention: Amiloride (Moduretic), Triamterene, Spironolactone (Aldactone, Uractone, Spirolang)
10. availability to participate in the study for 5 years
11. for women aged 55-69, negative mammography in the last 12 months

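### Expected events come from people aged 55 or more, but entry stops at 74 and excludes major disease, so deaths, cancers and cardiovascular events are probably overstated

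*Protocol*

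**What the plan says.** In the protocol's Methodology, under Analysis, item a) of the power computations bases the calculation "on expected mortality and ArCD incidence in the study area in men and women aged 55 or more". No upper age is given. A bracket adds that this was done "assuming the same age distribution as the general population". Item b) multiplies the rates by 1.5 for metabolic syndrome (3 for diabetes). Items c) to e) set the effect (25% or 33%), the average follow-up (3.5 years) and alpha (0.05). The result is 174 deaths, 175 cancers, 119 major cardiovascular events and 219 cases of diabetes.

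The eligible population is narrower:

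- **Age.** The Methodology inclusion criteria read "Age 55-74, waist circumference equal or greater than 85 cm for women and 100 cm for men". The Operative protocol repeats "age between 55 and 74", and the Background gives the same range.
- **Diabetes.** The exclusion criteria list "Diagnosed diabetes (or baseline fasting glycemia above 7mmol/L at baseline examination".
- **Cancer.** They also list "Cancer (except skin carcinoma) diagnosed in the last 5 years, or under treatment". The Operative protocol adds "for women aged 55-69, negative mammography in the last 12 months".
- **Cardiovascular disease.** The Operative protocol requires "no diagnosis of coronary heart disease, myocardial infarction, stroke, hearth failure".
- **Other.** Renal, cardiac, hepatic or respiratory insufficiency, neurodegenerative disease and marked frailty are also excluded.

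None of items a) to e) mentions a cut at age 74 or an adjustment for these exclusions.

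**The concern.** Read literally, item a) includes people aged 75 and over at their full population share, together with people who already have the diseases that bar entry. None of them can be randomised. For death, cancer, myocardial infarction and stroke, both differences would make the source rates too high for this cohort, provided that these rates rise with age and are lower in people screened free of disease. The only population adjustment described, the metabolic syndrome multiplier, raises the rates further.

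The stated powers follow almost entirely from these event counts, so an inflated count passes straight into them. The figures most exposed are the mortality and cancer powers, which are already only 69%, and the comparisons that involve a single arm of 500.

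**Working it through.** **Inputs from the Analysis section.** Cancers 175, cardiovascular events 119 and diabetes 219 give 175 + 119 + 219 = 513 composite events; deaths are 174. There are four arms of 500. Reductions are 33% or 25%, and alpha is 0.05, taken as two-sided because this reproduces the stated figures.

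**Follow-up.** (1,000 × 4 + 1,000 × 3) / 2,000 = 3.5 years, as stated.

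**Formula.** Two-proportion test with pooled variance, no continuity correction. Comparator risk is p0 = events/2,000 and p1 = p0 × (1 − reduction). Power = Φ[(p0 − p1 − 1.96 × SE0) / SE1], where SE0 is the pooled and SE1 the unpooled standard error.

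**Step 1: reproduce the plan.** p0 = 513/2,000 = 0.2565. At a 25% reduction p1 = 0.1924, the difference is 0.0641, SE0 = 0.01866 and SE1 = 0.01860. Power = Φ[(0.0641 − 0.0366)/0.01860] = 93.1%.

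| Comparison | 33%: reproduced (stated) | 25%: reproduced (stated) |
|---|---|---|
| 1,000 v 1,000 | 99.6 (99) | 93.1 (92) |
| 500 v 1,500 | 98.0 (97) | 84.1 (84) |
| 500 v 500 | 90.5 (89) | 68.1 (65) |
| Deaths, 174/2,000 = 0.087 | 69.6 (69) | – |
| Cancers, 175/2,000 = 0.0875 | 69.9 (69) | – |

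With a continuity correction, all six composite figures fall within 2 points of those stated. The arithmetic from counts to these powers is therefore sound, and the question is whether the counts are.

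**Step 2: what can be derived about the counts.** The protocol gives no age-specific rates and no rates in people without the excluded conditions. The counts can be neither rebuilt nor corrected from the document, so a range has to be assumed.

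**Step 3: illustration.** Assumption: cancer and cardiovascular events (175 + 119 = 294) are 20, 30 or 40% lower, and diabetes stays at 219.

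- 219 + 294 × 0.8 = 454, p0 = 0.227
- 219 + 294 × 0.7 = 425, p0 = 0.212
- 219 + 294 × 0.6 = 395, p0 = 0.198

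| Power (%) | Stated | 454 events | 425 events | 395 events |
|---|---|---|---|---|
| 1,000 v 1,000, 33% | 99 | 99 | 98 | 98 |
| 1,000 v 1,000, 25% | 92 | 89 | 86 | 83 |
| 500 v 1,500, 25% | 84 | 78 | 74 | 70 |
| 500 v 500, 33% | 89 | 86 | 83 | 79 |

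For deaths lower by 20, 30 or 40% (139, 122 or 104), power at a 33% reduction is 59, 53 or 47%, against 69% stated. Cancers lower by the same shares give 60, 54 or 47%.

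**The case against.** **The wording may be shorthand.** The phrase about age 55 or more could loosely mean the eligible range. If so, one line settles it; as written, it does not match the eligibility criteria.

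**A reader might infer that every event count and every power figure is overstated.** The documents do not support that. Diabetes is the largest component (219 of 513). Nothing in the protocol shows that new diabetes is commoner above 74, and removing people who already have diabetes does not by itself lower incidence among the rest. Cutting all 513 events by 20, 30 or 40% would give 85, 79 or 71% for 1,000 v 1,000 at a 25% reduction, but that applies to diabetes a fall that has not been shown.

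**A reader might also infer that the plan's own figures prove the error**, since 174/(2,000 × 3.5) is 2.49% mortality a year and deaths about equal cancers. Calling that too high needs an outside benchmark that the documents lack. The denominator is also unclear: the same sentence adds 200 persons, and 174/(2,200 × 3.5) is 2.26%.

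**Some features push the other way, and these stand as partial offsets.**

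- The 119 cardiovascular events cover only myocardial infarction and stroke, whereas the Follow-up section also counts acute coronary syndrome and coronary revascularisation as verified coronary disease.
- The plan leaves out person-time from the recruitment year. Under uniform entry (an assumption) that is 2 × 1,000 × 0.5 = 1,000 person-years beside 7,000, or 14%.
- The Background cites two-fold cardiovascular and five-fold diabetes risks with metabolic syndrome, above the multipliers of 1.5 and 3. The reference groups may differ, and no such figure is given there for cancer or death.

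None of these corrects the age and health basis of the rates. Only the omitted person-time bears on deaths and cancers.

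**Conclusion.** The point holds as a mismatch between the population behind the rates and the population that can enrol, with no correction described. It is a fault in an input assumption; the composite, mortality and cancer powers follow correctly from the counts given. Deaths, cancers and cardiovascular events are probably overstated. That rests on two assumptions outside the document: that their rates rise with age, and that they are lower in people screened free of disease. The amount cannot be derived, and no direction is established for diabetes.

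The consequences are uneven. In the illustrated range the two main factorial comparisons at a 33% reduction are hardly affected, and at 25% they stay above 80%. The combination comparisons lose more: 500 v 1,500 at 25% drops below 80%. Mortality and cancer lose most, to between about 60% and 47%.

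Separately, the stated diabetes powers (98% at 33%, 85% at 25%) do not follow from 219/2,000, which gives 80% and 55%. The age basis does not explain that gap.

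**What to change.** 1. State the upper age used in item a), and whether the exclusions were reflected in the rates.
2. Recompute items a) and b) from the same study-area sources for entry ages 55-74, following attained age through follow-up. Someone who enters at 74 contributes person-time to about 78, so simply cutting the rate table at 74 would bias the counts downwards.
3. Use first-event rates in people without the excluded conditions. If the sources cannot supply them, give a stated range of reductions.
4. Restate the expected deaths, cancers, cardiovascular events and diabetes cases, and all powers in the Analysis section that depend on them.

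The cost is re-running an existing calculation. Stated power is likely to become somewhat less favourable, mainly for mortality, cancer and the combination comparisons. This change requires no alteration to the design or eligibility.

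### The 98% (85%) power stated for diabetes does not follow from the 219 expected cases, which give about 80% (55%)

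*Protocol*

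**What the plan says.** All the figures are in the Protocol, Methodology, under Analysis (power computations).

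- Event counts: "we would expect about 174 deaths, 175 cancers, and 119 major cardiovascular events (myocardial infarction and stroke"), and then "219 cases of diabetes, summing up to over 500 incident cases of major ArCD". These are counts for the whole recruited group.
- Assumptions: "alpha error = 0.05", with no test or sidedness named; the hypothesis that "the planned interventions may reduce ArCD incidence by 25 or 33" per cent; and an average follow-up of 3.5 years.
- Allowance for attrition: "plus 200 persons to compensate the power loss due to expected attrition".
- Composite of cardiovascular disease, diabetes and cancer, for a 33% (25%) reduction: 99% (92%) for 1,000 against 1,000, 97% (84%) for 500 against 1,500, and 89% (65%) for 500 against 500.
- Single outcomes, introduced by "Comparing 1,000 treated and 1,000 non-treated persons": 69% for a 33% difference in deaths or in cancer and, for diabetes, "98% power to detect a 33% difference in the cumulative incidence of diabetes (85% for 25% reduction").

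**The concern.** The diabetes power is almost as high as the composite power (98% and 85%, against 99% and 92%), although diabetes supplies only 219 of the 513 composite events. In the same sentence, 174 deaths or 175 cancers give 69%. Going from 175 to 219 events, a quarter more, cannot raise power from 69% to 98% with the same effect, group sizes and error rate.

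Diabetes incidence is a listed secondary outcome and the largest component of the primary composite. The sentence presents it as the one single disease for which the trial is well powered even at a 25% reduction. A reader who trusts it would take a null diabetes result as good evidence against a 25% effect.

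**Working it through.** **Inputs.** Expected events: 174 deaths, 175 cancers, 119 cardiovascular, 219 diabetes; 175 + 119 + 219 = 513, which agrees with the total of over 500. Groups: 1,000 and 1,000. Relative risks: 0.67 and 0.75. Alpha 0.05, taken as two-sided.

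**Formula.** With control rate p1 = events / 2,000, p2 = RR × p1 and p̄ the average rate across both groups (weighted by size when they are unequal):

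SE0 = √[p̄(1 − p̄)(1/n1 + 1/n2)], SE1 = √[p1(1 − p1)/n1 + p2(1 − p2)/n2]

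power = Φ[(p1 − p2 − 1.96 × SE0) / SE1]

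**Step 1: reproduce the other stated powers.**

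| Outcome and comparison | Events used | Computed, 33% (25%) | Stated |
|---|---|---|---|
| Deaths, 1,000 v 1,000 | 174 | 69.6% | 69% |
| Cancer, 1,000 v 1,000 | 175 | 69.9% | 69% |
| Composite, 1,000 v 1,000 | 500 | 99.5% (92.3%) | 99% (92%) |
| Composite, 500 v 1,500 | 500 | 97.7% (82.8%) | 97% (84%) |
| Composite, 500 v 500 | 500 | 89.5% (66.7%) | 89% (65%) |

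All agree within about 2 points, so this is in effect the Protocol's own method.

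**Step 2: apply it to diabetes.** p1 = 219 / 2,000 = 0.1095.

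- 33% reduction: p2 = 0.0734, difference 0.0361, SE0 = 0.01289, SE1 = 0.01286. Power = Φ(0.845) = 80.1%, against 98% stated.
- 25% reduction: p2 = 0.0821, difference 0.0274, SE0 = 0.01316, SE1 = 0.01315. Power = Φ(0.120) = 54.8%, against 85% stated.

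**Step 3: try other readings of the 219.**

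| Reading | 33% | 25% |
|---|---|---|
| 219 of 2,200, with 1,100 per group | 79.7% | 54.4% |
| Continuity correction | 77.9% | 51.7% |
| Log-rank (Schoenfeld) | 77.3% | 51.2% |
| One-sided 5% | 87.7% | 66.8% |
| 219 is the total after the treatment effect | 87.3% | 61.1% |
| The same, one-sided | 92.8% | 72.4% |
| All 219 in one control group of 1,000 | 98.7% | 87.6% |

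No whole-trial reading reaches 98% (85%). One-sided testing is excluded in any case, because it would give about 80% for cancer instead of the stated 69%. Only the last row comes close. It fails because the 219 is added to 175 and 119 to form a whole-trial total, and because the same treatment of 175 cancers would give about 96%, not 69%.

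**Step 4: which figure is wrong?** Solving the formula for p1 gives about 0.205 for both stated powers, or 0.205 × 2,000 ≈ 410 cases. The composite would then be 175 + 119 + 410 = 704 events. With 704 events the comparison of 500 with 500 would have about 98% (86%) power, against 89% (65%) stated, and 1,000 against 1,000 would have about 99% for a 25% reduction, against 92% stated. The composite powers therefore rest on 219.

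**The case against.** The case on the other side is about weight and precision; it does not rescue the stated figure.

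- Diabetes incidence is one of several secondary outcomes. The main outcome is total incidence of age-related chronic disease, and its powers reproduce from the stated events. The diabetes sentence sets no sample size, decision rule or analysis. This is right, and it limits the consequence to how the diabetes result is planned for and read.
- The near match when all 219 cases are put in one group suggests a slip confined to one sentence. That is a plausible origin, though the document does not confirm it. It explains the error without removing it.
- The Protocol names neither test nor sidedness, and does not say whether 219 is before or after the treatment effect. The values of 80% and 55% therefore depend on a method inferred from the other figures. This also stands: they should be read as approximate. Under the readings of 219 as a whole-trial count shown above, the range is about 77% to 93% (51% to 72%), still below 98% (85%).

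**Conclusion.** The stated diabetes power is wrong as written. On the method that reproduces the section's other powers, 219 cases give about 80% for a 33% reduction and 55% for a 25% reduction. Compared like for like, the chance of missing a true 33% reduction is about 20% instead of 2%, and of missing a true 25% reduction about 45% instead of 15%.

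This assumes a two-sided 5% test and that 219 is a whole-trial count without treatment effect; the agreement for deaths, cancer and the composite supports both. The composite powers and the planned sample size are unaffected unless 219 itself proves wrong, and the composite figures speak against that.

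**What to change.** Restate the diabetes power as about 80% for a 33% reduction and about 55% for a 25% reduction, and name the test and its sidedness so that the figures can be reproduced.

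Before doing so, check 219 against the incidence data behind it. If the source shows that 219 is the error, correct it together with the total of over 500 and every power that depends on that total.

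The cost is one corrected sentence and a less favourable figure. Recruitment, treatment, follow-up and analysis do not change.

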## Operative protocol

### First meeting

**Illustration of the study design, check of inclusion criteria, registration of potentially eligible volunteers, informed consent signature, and arrangement of meeting dates for clinical visit and blood sample**

#### Inclusion criteria:

1. waist circumference > 85 cm for women and >100 cm for men
2. age between 55 and 74
3. no diagnosis of cancer in the last 5 years (except skin carcinomas)
4. no diabetes (IDDM and NIDDM),
5. no kidney insufficiency
6. no acute or chronic hepatitis
7. no diagnosis of coronary heart disease, myocardial infarction, stroke, hearth failure
8. no neurodegenerative disease
9. not under treatment with the following drugs:
  - Cimetidine, Ranitidine
  - Sulfamethoxazole + Trimetoprim (Bactrim, Chemitrim, Eusaprim)
  - Nifedipine (Adalat, Nifedidor, Nifasal, Nipin, Fenidina, Euxat, Coral, Citilat)
  - Furosemide (Lasix)
  - Diuretics with K retention: Amiloride (Moduretic), Triamterene, Spironolactone (Aldactone, Uractone, Spirolang)
10. availability to participate in the study for 5 years
11. for women aged 55-69, negative mammography in the last 12 months

### Second meeting

**Clinical visit (including breast examination for women), anthropometric measurements, collection of blood and urine samples**

### Third meeting

**Final eligibility check on the basis of blood and urine examinations**

#### Further inclusion criteria:

- 1) fasting glycemia <126 mg/dl
- 2) serum creatinin <124 µmol/L
- 3) Proteinuria absent or traces (1+)
- 4) Presence of metabolic syndrome (waist circumference + two further traits)

**At this point eligible participants are invited to start taking metformin 425 mg day (half a pill) for 15 days and 850 mg/day (a single full pill) for the subsequent 15 days**

The meeting will include:

- clinical visit
- explanation on how to take the pills:
  - in the first 15 days the participant must take half a pill (425mg) of metformin per day, during a main meal (breakfast, lunch or dinner)
  - in the subsequent 15 days the participant must take a full pill (850mg) of metformin per day, during a main meal (breakfast, lunch or dinner)
- discussion of the possible side effects and invitation to contact the study physician, available 24h/24, in case of symptoms or questions
- if the participant miss taking one or more pills, he/she must not increase the dose in the following days, and must not throw away the unused pills, which must remain in the box and rendered to the study centre at the next meeting
- arrangement of the next meeting (after 30 days)
- each participant is given a leaflet with instructions

**Fourth meeting****Evaluation of compliance and side effects to complete the eligibility**

30 days after the start of metformin treatment, the physician will check the participant's compliance through

- a) the counting of residual pills
- b) specific questions on side effects and on willingness to continue

**Participants having demonstrated an adequate compliance and no or trivial side effects will be randomized**

## **RANDOMIZATION**

**Fifth meeting:**

**Participants assume a placebo or metformin (850 mg) pill per day for 30 days.**

The physician will:

- Provide the pills for the next 30 days
- Remember not throwing away the unused pills
- Arrange the next meeting (that will be also remembered through an SMS)
- Arrange the dates of kitchen courses for participants randomized in the active lifestyle intervention group

